## ABBREVIATIONS

|    |            |
|----|------------|
| Ab | Antibodies |
| Ad | Adenovirus |

---

|                            |                                                                    |
|----------------------------|--------------------------------------------------------------------|
| AdvantageEDC SM | The EMMES Corporation's web-based data entry system                |
| AE                         | Adverse Event/Adverse Experience                                   |
| CFR                        | Code of Federal Regulations                                        |
| CMI                        | Cell Mediated Immunity                                             |
| CRF                        | Case Report Form                                                   |
| CS                         | Circumsporozoite                                                   |
| DCC                        | Data Coordinating Center                                           |
| DHHS                       | Department of Health and Human Services                            |
| DMID                       | Division of Microbiology and Infectious Diseases, NIAID, NIH, DHHS |
| eCRF                       | Electronic Case Report Form                                        |
| ELISA                      | Enzyme-linked immunosorbent assay                                  |
| FDA                        | Food and Drug Administration                                       |
| GCP                        | Good Clinical Practice                                             |
| HIPAA                      | Health Insurance Portability and Accountability Act                |
| ICH                        | International Conference on Harmonisation                          |
| ICMJE                      | International Committee of Medical Journal Editors                 |
| IEC                        | Independent or Institutional Ethics Committee                      |
| IND                        | Investigational New Drug Application                               |
| IRB                        | Institutional Review Board                                         |
| ISM                        | Independent Safety Monitor                                         |
| MedDRA ®        | Medical Dictionary for Regulatory Activities                       |
| MOP                        | Manual of Procedures                                               |
| NIAID                      | National Institute of Allergy and Infectious Diseases, NIH, DHHS   |
| NIH                        | National Institutes of Health                                      |
| PI                         | Principal Investigator                                             |
| PE                         | Physical Examination                                               |
| PBMC                       | Peripheral Blood Mononuclear Cells                                 |
| SAE                        | Serious Adverse Event/Serious Adverse Experience                   |
| SMC                        | Safety Monitoring Committee                                        |
| US                         | United States                                                      |
| vp                         | Viral particles                                                    |

---

## PROTOCOL SUMMARY

**Title:** A Phase 1 Randomized, Controlled, Double-Blinded, Dosage-Escalation Trial to Evaluate the Immunogenicity, Safety, and Reactogenicity of an Adenovirus Type 35 Based Circumsporozoite Malaria Vaccine in Burkina Faso, Semi-Immune, Healthy Adults 18 to 45 Years of Age.

**Phase:** I

**Population:** 48 healthy male and female subjects aged 18 to 45 years in Burkina Faso.

**Site:** Projet de Développement de Vaccins Anti-Paludique- Centre National de Recherche et de Formation sur le Paludisme (PDVAP/CNRFP) Burkina Faso

**Study Duration:** Approximately 12 months per subject .

**Description of Agent or Intervention:** Adenovirus Type 35 Circumsporozoite Malaria Vaccine (Ad35.CS.01) versus Normal Saline Placebo Control via Intramuscular Injection.

### Objectives:

#### Primary Objectives:

- To assess the safety and reactogenicity of ascending dosages of Adenovirus Type 35 based circumsporozoite malaria vaccine among healthy, semi-immune, subjects given in 3 intramuscular doses at 0, 1 and 3 months.

#### Secondary Objectives:

- To evaluate the immunogenicity of the Adenovirus Type 35 based circumsporozoite malaria vaccine through performance of Humoral Immune Assays (ELISA [enzyme-linked immunosorbent assay] for antibodies to circumsporozoite antigen and Adenovirus Neutralization Assay for neutralizing antibodies to Adenovirus type 35) and Cellular Immune Assays (Elispot and Flow Cytometry) for CS-specific CD4+ and CD8+ T cell responses and a whole blood ELISA assay to measure secreted cytokines.

#### Exploratory Objectives:

- To evaluate the immunogenicity of the Adenovirus Type 35 based circumsporozoite malaria vaccine through performance of Cellular Immune Assays (Elispot and Flow

Cytometry) for CS-specific CD4+ and CD8+ T cell responses and a whole blood ELISA assay to measure cytokines

### Description of Study Design:

Subjects will receive 3 doses of the vaccine by the intramuscular route at 0, 1 and 3 months. The safety, reactogenicity and immunogenicity of ascending dosages of the vaccine will be assessed. Ten subjects will receive vaccine at each of the following dosage levels: 10^9 viral particles (vp)/mL, 10^10 vp/mL, 5 x 10^10 vp/mL and 10^11vp/mL. Two subjects in each group will receive normal saline as placebo control in each dose group. Dosage escalation will proceed only after review of the safety data by the SMC of the prior dosage level.

| Group | Vaccine Formulation
Ad35.CS.01 | Number of
Vaccine/Placebo |
|-------|-----------------------------------|------------------------------|
| A     | 10  vp/mL             | 10/2                         |
| B     | 10  vp/mL            | 10/2                         |
| C     | 5 x 10  vp/mL        | 10/2                         |
| D     | 10  vp/mL            | 10/2                         |
| Total |                                   | 40/8                         |

### Outcome Measures:

#### Primary:

- The number of subjects experiencing severe (Grade 3) solicited injection site reactions within 14 days following vaccination.
- The number of subjects experiencing severe (Grade 3) solicited systemic reactions within 14 days following vaccination.
- The number of subjects spontaneously reporting severe (Grade 3) adverse events considered associated with the vaccination at any point during the study period.
- Serious adverse events considered associated with the vaccination reported at any point during the study period.

#### Secondary:

- Antibody titers against the malaria circumsporozoite antigen at days 0, 28, 56, 84, 112 and 140 (Geometric Mean Titer and individual log ELISA units).

- Neutralizing antibody titers against Adenovirus type 35 by Adenovirus Neutralization Assay (GMT).1

Exploratory:

- T cell responses against the malaria circumsporozoite antigen by Elispot at days 0, 28, 56, 84, 112 and 140 .
- T cell responses against the malaria circumsporozoite antigen by Flow Cytometry at days 0, 28, 56, 84, 112 and 140.
- T cell responses against the malaria circumsporozoite antigen by a whole blood assays to measure secreted cytokines.

## 2 BACKGROUND INFORMATION AND SCIENTIFIC RATIONALE

### 2.1 Background Information

Malaria currently represents one of the most prevalent infections in tropical and subtropical areas throughout the world. Each year, malaria affects around 300 million people and kills 1 to 3 million people in developing countries. Malaria is the leading cause of death in children in sub-Saharan Africa, and drug-resistant parasites and insecticide-resistant vectors increasingly pose challenges for malaria control programs. Other factors include environmental and climatic changes, civil disturbances and increased mobility of populations.

Malaria is caused by the mosquito-borne hematoprotzoan parasites belonging to the genus *Plasmodium*. Four species of *Plasmodium* protozoa (*P. falciparum*, *P. vivax*, *P. ovale* and *P. malariae*) are responsible for the disease in man; many other species cause disease in animals, such as *Plasmodium yoelii* and *Plasmodium berghei* in mice. *P. falciparum* accounts for the majority of infections in man and is the most lethal ("tropical malaria").

Malaria parasites have a life cycle consisting of several stages. Each one of these stages is able to induce specific immune responses against the corresponding stage-specific antigens. Malaria parasites are transmitted to man by several species of female *Anopheles* mosquitoes. Infected mosquitoes inject the sporozoite form of the malaria parasite into the mammalian bloodstream. Before invading hepatocytes, sporozoites remain for a few minutes in the circulation. At this stage the parasite is located in the extracellular environment and is exposed to antibody attack, mainly directed to the circumsporozoite (CS) protein, a major component of the sporozoite surface. Once in the liver, the parasites replicate and develop into schizonts (up to 20,000 per infected cell). During this intracellular stage of the parasite, the main effectors of the host immune response are T lymphocytes, especially CD8+ T cells [1].

Radiation-attenuated sporozoites have been shown to provide protective immunity against malaria, in experimental animal models as well as in humans [2,3]. This vaccine elicits both sporozoite-neutralizing antibodies as well as potent cell-mediated immunity, but it is technically difficult to manufacture [4].

Compelling evidence has been obtained over the last 17 years that CD8+ T cell immunity is as important, if not more important, than B-cell immunity for protection against the liver stages of malaria [5,6,7].

Ad35.CS.01 is a malaria vaccine for which a codon optimized nucleotide sequence representing the *P. falciparum* circumsporozoite (CS) surface antigen is inserted in a replication deficient Adenovirus 35 backbone. It was manufactured by Crucell Holland BV, Leiden, the Netherlands..

### **2.1.1 Pre-Clinical and Toxicology Studies**

#### **New Zealand White Rabbits:**

A 99-day toxicology study, adherent to Good Laboratory Practice, was conducted in 60 New Zealand White rabbits using Ad35.CS.01 (manufactured adhering to Good Manufacturing Practice) or placebo given intramuscularly in four IM administrations. Twenty rabbits in each of three cohorts received  $1.2 \times 10^{10}$  vp per 1 mL dose of Ad35.CS.01,  $1.2 \times 10^{11}$  vp per 1 mL dose of Ad35.CS.01, or 1 mL of placebo consisting of formulation buffer. There was no effect on mortality, clinical observations, cageside observations, dermal Draize observations, body weight changes, ophthalmologic examinations, hematological parameters, coagulation parameters, gross pathology findings, or organ weights. Changes in clinical chemistry parameters were not of clinical significance or not test article related. There was no evidence of systemic toxicity with the exception of a transient effect on food consumption in the high-dose group. Pathology findings included test article-related histological effects seen at the injection sites considered to represent host inflammatory responses to antigen administration.

A 90-day biodistribution study, adherent to Good Laboratory Practice, was conducted with a single 1 mL IM administration of  $1.2 \times 10^{11}$  vp of Ad35.CS.01, or placebo, to 30 and 12 New Zealand White rabbits, respectively. The TaqMan qPCR assay used to measure the biodistribution and persistence of the Ad35.CS.01 vaccine demonstrated that Ad35.CS.01 DNA remained primarily localized in the muscle and skin at the injection site with the exception of a few copies detected in the spleens of 6 of 10 rabbits at study day 9. Copy numbers detected in the spleen were 63 and 55 per microgram of genomic DNA, and 4 others that were too low to quantify. The vector did persist at the muscle and skin at the site of injection from study days 9 through 91, but the vector copy number decreased markedly over that period.

#### **Non-human Primates:**

A non-GLP (Good Laboratory Practice) immunogenicity and safety study of Ad35.CS was performed in 18 adult rhesus macaques. Seven primates each received  $1 \times 10^{11}$  vp of Ad35.CS IM on either a 0, 3 month or 0, 6 month schedule. Four control primates received Ad35 without the transgene as control. Safety assessments included twice daily visual inspections, and clinical examinations of spleen, lymph nodes, joints, and injection site (using the contralateral site for comparison) and measurement of body weight and vital signs on the day of vaccination (day 0) and on days 1, 2, 3, 7, and 14 after each injection.

Clinical laboratory determinations (selected serum chemistries and complete blood counts) were done on the same schedule as the clinical examinations and at specified additional times, which extended for all animals to six months after the last test article injection. These inspections and examinations did not reveal systemic toxicities. Increases in White Blood Cell counts were recorded 24 hours after the first vaccinations in the two test article groups. Occasional elevations were observed in some animals in ALT and GGT over the course of the study, but these elevations were mild, transient, and did not appear to be related to the test article or dosing schedule. At 2 weeks, 3 months, and 6 months after final vaccinations, sera were collected for analysis of CS-specific antibody responses by ELISA and peripheral blood mononuclear cells were harvested for ELISPOT analysis. At all time points and with both assays, Ad35.CS generated significantly higher immune responses than the control agent. Refer to the clinical Investigator's Brochure for details of the immunogenicity responses in the primate study, as well as another study demonstrating immunogenicity of a single IM dose of  $1 \times 10^9$  vp or  $1 \times 10^{10}$  vp of Ad35.CS.01 in mice.

### **2.1.2 Clinical Experience**

A Phase 1 randomized, controlled, dosage-escalation trial to evaluate the immunogenicity, safety and reactogenicity in healthy adults 18 to 45 years of age is ongoing in the U.S. Seventy two subjects are randomized in a 5:1 ratio to receive vaccine or normal saline placebo control by the IM route at 0, 1 and 6 months. Fifteen subjects have received vaccine at  $10^8$  vp/mL, 15 subjects have received vaccine at  $10^9$  vp/mL, and 15 subjects have received vaccine at  $10^{10}$  vp/mL. Enrollment of subjects receiving vaccine at  $10^{11}$  vp/mL is ongoing.

One SAE, not associated with vaccination, has been reported; it was a small bowel obstruction related to appendectomy for appendicitis. It resolved without sequelae.

All mild and moderate AEs associated with injection resolved without sequelae. A causal association with vaccine cannot be determined, and the safety data have not been unblinded at this time. There were a total of 5 moderate AEs in 4 subjects associated with time of injection: a right sided paresthesia lasting 24 hours, itchy tongue which resolved, brachial plexopathy lasting 24 hours, anemia (iron deficiency) and diaphoresis which resolved the same day.

In the current ongoing study in the U.S., after evaluation of the first 6 participants of Group  $10^{11}$  vp/mL, it was noted that significant reactions (grade 3) occurred in 2 of the 6 and were considered associated with injection. Symptoms began in the first 8 hours following vaccination, but none occurred in the first 4 hours following vaccination. These symptoms included fever, chills, myalgia, nausea and GI side effects such as diarrhea, that occasionally lasted for several days, was self-limited, and may or may not have been related to the vaccine.

Two individuals, one from Group  $10^8$  vp/mL and one from Group  $10^{11}$  vp/mL, developed Grade 2 signs and symptoms consistent with a brachial plexus neuropathy that was deemed associated with vaccination. For the subject in Group  $10^8$  vp/mL, symptoms began on the day of vaccination for both the 2nd and 3rd vaccinations but resolved within 24 hours without sequelae. For the subject in Group  $10^{11}$  vp/mL, symptoms began within the first week after 2nd vaccination and were resolved by the Day 7 physical examination. Both of these events resolved without sequelae.

## 2.2 Rationale

It is hypothesized that the Ad35.CS.01 vaccine will prevent the *P. falciparum* parasite, which causes malaria, from entering and developing within the liver of those who become infected. Ad35.CS.01 would therefore be expected to reduce malaria-attributable morbidity and mortality.

## 2.3 Potential Risks and Benefits

### 2.3.1 Potential Risks

Adenovirus Type 35 circumsporozoite vaccine has been administered only in a malaria naïve population in a Phase 1 trial in the US, but not yet in semi-immune human subjects. Therefore, the safety of the vaccine in a population that is semi-immune to malaria has yet to be established. An adenovirus Type 35 vaccine with an insert from *Mycobacterium tuberculosis* has been tested in phase I clinical trials and showed no safety concerns in 94 volunteers immunized to date.

A test-of-concept study of an adenovirus type 5 HIV vaccine (the STEP trial: [www.hvtn.org](http://www.hvtn.org).) has been discontinued for enrollment after the interim analysis showed that vaccine did not prevent HIV infection or change a course of disease. In this trial a potential safety signal has been identified: there were more HIV infections in male participants who received the vaccine than in those who received placebo. Male participants who had higher level of pre-existing antibodies to adenovirus type 5 and engaged in high risk sexual behavior showed a higher incidence of HIV infections. The study was not powered to determine the etiology of these findings. Further analyses are under way to address this potential safety signal.

The risk for participants in this trial (adenovirus type 35 based vector with a malaria gene insert) is theoretically low since it is not clear whether the safety signal is a statistical or biological phenomenon and whether, if shown to be a biological phenomenon, it will apply to other adenoviral vector vaccines, particularly those with non-HIV related inserts, administered to individuals who are not at increased risk of HIV exposure. In addition, Ad35 serotype infection is rare in Africa, and thus, pre-existing immunity is rare.

Additional discomforts of this study are those of having blood drawn from an arm vein, IM injection of the vaccine, and possible reactions to the vaccine. Drawing blood causes transient discomfort and may cause fainting. Infection at the site where blood will be drawn or where the vaccination is given is extremely unlikely, but is a potential risk. Bruising at the site of blood drawing may occur, but can be prevented or lessened by applying pressure for several minutes immediately after the blood draw. Intramuscular injection may cause injection site pain, swelling, and redness. Immediate allergic reactions to vaccine, including anaphylaxis, are in general extremely rare (approximately 1 person in 4,000,000), and might occur as a skin rash such as hives, difficulty breathing, fainting, drop in the blood pressure and death. Such reactions can usually be stopped by emergency medications administered by study personnel. Vaccine recipients may develop systemic reactions such as fever, headaches, body aches, and fatigue. These reactions are usually greatest within the first 24 to 72 hours after vaccination and last 1 to 2 days. Analgesics (e.g., aspirin or Tylenol®) and rest will generally relieve or moderate these symptoms. Other hypersensitivity reactions, including Arthus reactions resulting in large local swelling reactions, are also possible.

In the ongoing Ad35.CS.01 Phase 1 study in the U.S., after evaluation of the first 6 participants of Group D, it was noted that significant reactions (grade 3) occurred in 2 of the 6 and were considered associated with vaccination. Symptoms began in the first 8 hours following vaccination, but none occurred in the first 4 hours following vaccination. These symptoms included fever, chills, myalgia, nausea and GI side effects such as diarrhea, which occasionally lasted for several days, were self-limited, and may or may not have been related to the vaccine. In addition, two individuals, one from Group A and one from Group D, developed signs and symptoms consistent with a Grade 2 brachial plexus neuropathy that was deemed associated with vaccination. For the subject in Group A, symptoms began on the day of vaccination for both the 2nd and 3rd vaccinations but resolved within 24 hours without sequelae. For the subject in Group D, symptoms began within the first week after 2nd vaccination and were resolved by the Day 7 physical examination.

### **2.3.2 Known Potential Benefits**

There are no direct benefits to subjects from participating in the study. However, subjects may benefit altruistically by the knowledge that they are aiding in the malaria vaccine development effort. They may also receive medical attention beyond that which they normally receive, including the screening medical examination, periodic clinical laboratory examinations, and referral for treatment for medical problems that arise during the study. In addition, medical treatment will be provided for malaria illness for all volunteers during the study period, regardless of study-relatedness.

## **3 OBJECTIVES**

### **3.1 Study Objectives**

The primary objective is to assess the safety and reactogenicity of four ascending dosages of Adenovirus 35 circumsporozoite malaria vaccine among healthy, semi-immune, subjects given in 3 doses at 0, 1 and 3 months by IM injection.

The secondary objective is to evaluate the immunogenicity of 3 doses of Adenovirus 35 circumsporozoite malaria vaccine at 4 dosage levels by measuring antibodies against the circumsporozoite antigen by ELISA, neutralizing antibodies against Adenovirus type 35, and T-cell response against the circumsporozoite antigen by cellular immune assays.

### **3.2 Study Outcome Measures**

#### **3.2.1 Primary Outcome Measure**

- The number of subjects experiencing severe (Grade 3) solicited injection site reactions within 14 days following vaccination.
- The number of subjects experiencing severe (Grade 3) solicited systemic reactions within 14 days following vaccination.
- The number of subjects spontaneously reporting severe (Grade 3) adverse events considered associated with the vaccination at any point during the study period.
- Serious adverse events considered associated with the vaccination reported at any point during the study period.

#### **3.2.2 Secondary Outcome Measures**

- Antibody titers against the malaria circumsporozoite antigen at days 0, 28, 56, 84, 112 and 140 (Geometric Mean titer and individual log ELISA units).
- Neutralizing antibody titers against Adenovirus type 35 by Adenovirus Neutralization Assay at days 0, 28, 56, 84, 112 and 140 (GMT).

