## 5 STUDY POPULATION

The study will be carried out by the PDVAP/CNRFP in the Saponé health district in the Bazèga province. This rural area is situated 50 km south west of Ouagadougou, the capital city of Burkina Faso in the Sudan-Sahelian eco-climatic zone. The PDVAP/CNRFP has been conducting epidemiological studies in the area last year. A vaccinology unit specifically dedicated for vaccine trials has been built. The PDVAP/CNRFP has further established demographic surveillance system within Saponé health district (87,678 inhabitants living 79 villages around Balonghin). Through this system, data on vital events and basic malariometric parameters have been collected for a deeper and reliable baseline data necessary for potentials malaria phase 1, 2 or 3 vaccines trials.

In this area malaria transmission is markedly seasonal and intense during the rainy season from June to October. The entomological inoculation rate is above one infective bite/person/night during the intense transmission season and drops to 0 during the low season (dry season). The main malaria vectors are *Anopheles gambiae*, *An. Arabiensis* and *An. funestus*. *P falciparum* accounts for about 90% of malaria infections. The first line treatment for uncomplicated malaria in Burkina is Artemether-Lumefantrine or Artesunate-Amodiaquine. Bed nets are rarely used in the DSS area with less than 5% of the population owning a net.

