## 11 STATISTICAL CONSIDERATIONS

### 11.1 Study Overview

The primary objective of the study is to assess the safety and reactogenicity of ascending dosages of Adenovirus Type 35 Based circumsporozoite malaria vaccine among healthy subjects given in 3 intramuscular doses at 0, 1 and 3 months. The secondary objective of the study is to evaluate the immunogenicity of the Adenovirus Type 35 based circumsporozoite malaria vaccine through performance of humoral immune assays (ELISA for Ab vs. CS and Adenovirus Neutralization Assay for neutralizing Ab against Ad35) and cellular immune assays.

The primary outcome measure is the frequency and severity of injection site and systemic AEs. These variables will be analyzed descriptively by:

1. The number of subjects experiencing severe (Grade 3) injection site reactions within 14 days following vaccination.
2. The number of subjects experiencing severe (Grade 3) systemic reactions within 14 days following vaccination.
3. The number of subjects with severe or life-threatening adverse reactions considered associated with the vaccination at any point during the study period.

The secondary outcome measures are:

1. Antibody titers against the malaria circumsporozoite antigen at days 0, 28, 56, 84, 112 and 140 (Geometric Mean Titer and individual log ELISA units).
2. Neutralizing antibody titers against Adenovirus type 35 by Adenovirus Neutralization Assay at days 0, 28, 56, 84, 112 and 140.

The exploratory outcome measures are:

1. T cell responses against the malaria circumsporozoite antigen by Elispot.
2. T cell responses against the malaria circumsporozoite antigen by Flow Cytometry
3. Cytokine responses against the malaria circumsporozoite antigen by ELISA after whole blood stimulation.

We propose to confirm the safety of the new vaccine by assessing safety and reactogenicity of the vaccine at 14 days after the initial dose in the lower dosages before escalating to the next

dosage level. Dosage level groups will include 10 subjects given vaccine and 2 subjects given normal saline placebo control intramuscularly.

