### **Sample Size Considerations**

The sample size of 10 per group is selected to obtain preliminary safety information on a small cohort of subjects before proceeding to larger trials. If there are adverse events associated with vaccination in this population, this study will have approximately 80% probability to observe at least one such event in a study size of 10 if the true rate is 10%. If there are no adverse events associated with the vaccine, the upper bound for the one-sided 95% confidence interval will be 18% for a study size of 10. The proposed sample size will provide pilot data on secondary outcomes and will not assure adequate power to reject secondary hypothesis of dose-related immunogenic response unless that response is very large.

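### For CS antibody the protocol names only titer levels by day; a fold-rise from Day 0 and Day-0-adjusted GMTs would keep baseline differences out of the dose-group picture at almost no cost

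*Protocol*

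**What the plan says.** Protocol section 3.2.2 defines the CS antibody outcome as titers at days 0, 28, 56, 84, 112 and 140, summarised as "Geometric Mean titer and individual log ELISA units". Section 11.1 repeats it: "Antibody titers against the malaria circumsporozoite antigen at days 0, 28, 56, 84, 112 and 140", again as "Geometric Mean Titer and individual log ELISA units". The Protocol Summary agrees. No section names a ratio to Day 0, a change from Day 0, a response definition or a baseline adjustment.

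The setting is described in these places:

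- Section 3.1: the vaccine is studied "among healthy, semi-immune, subjects given in 3 doses at 0, 1 and 3 months by IM injection".
- Section 5: "In this area malaria transmission is markedly seasonal and intense during the rainy season from June to October", and "The entomological inoculation rate is above one infective bite/person/night during the intense transmission season", falling to zero in the dry season.
- Section 2.1: CS is the main target of antibody against sporozoites.
- Section 5.5.1: randomization is between vaccine and placebo only. Section 7.2: groups are filled A to D in sequence.
- Section 8.2.2.1: serum for the humoral assays is drawn at Day 0, before the first dose.
- Section 11.2: the analysis is descriptive, with 95% confidence intervals. Comparisons of secondary outcomes with controls are optional and no method is fixed.
- Sample Size Considerations: the trial "will not assure adequate power to reject secondary hypothesis of dose-related immunogenic response" unless that response is very large.

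**The concern.** The secondary objective is immunogenicity at each of four dosage levels. In malaria-naive adults a post-vaccination GMT would come close to answering that. In adults with long natural exposure, some CS antibody before dose 1 is to be expected. A GMT at Day 56 or Day 112 then combines pre-existing antibody with the vaccine response.

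This matters most when dose groups are set side by side. Each has 10 vaccinees, and randomization does not balance them against each other. They also start at different calendar times in an area where exposure depends on the season. One group may show a higher later GMT than another partly because it started higher. The Day 0 titer that could remove much of this is already collected, but the named summaries do not use it for that purpose.

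**Working it through.** **The plan's own figure.** There is none for this outcome. The figures under Sample Size Considerations concern adverse events only. The SDs and correlations below are assumptions, shown as ranges.

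**How far apart the dose groups start (sections 5.2 and 15.4).** These are minimum waits, with no time allowed for committee review.

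- Group A: 2 subjects on Day 0, then 4, 4 and 2 at two-day intervals, so the last first dose falls on Day 6.
- Group B: 14-day data after all Group A first doses, 6 + 14 = Day 20. The second six follow on Day 22.
- Group C: 22 + 14 = Day 36. The second six follow on Day 38.
- Group D: 38 + 14 = Day 52.

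Group D therefore starts at least 52 days, about seven weeks, after Group A.

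**Chance difference in Day 0 GMT.** The SE of the difference in mean log10 titer is SD × √(1/n₁ + 1/n₂). The fold difference at one SE is 10^SE, and the 95% limit is 10^(1.96 × SE).

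| Comparison | Assumed log10 SD | SE | One SE | 95% limit |
|---|---|---|---|---|
| 10 v 10 (two dose groups) | 0.3 | 0.134 | 1.36-fold | 1.83-fold |
| 10 v 10 (two dose groups) | 0.5 | 0.224 | 1.67-fold | 2.74-fold |
| 10 v 8 (dose group v pooled placebo) | 0.3 | 0.142 | 1.39-fold | 1.90-fold |
| 10 v 8 (dose group v pooled placebo) | 0.5 | 0.237 | 1.73-fold | 2.92-fold |

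**What carries into a later GMT.** These are differences at Day 0, not distortions at Day 56 or 112. With equal SDs at both days, the expected carry-over on the log scale is rho times the Day 0 difference, or 10^(rho × SE) at one SE. For two groups of 10:

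| Assumed rho | SD 0.3 | SD 0.5 |
|---|---|---|
| 0.3 | 1.10-fold | 1.17-fold |
| 0.5 | 1.17-fold | 1.29-fold |
| 0.7 | 1.24-fold | 1.43-fold |

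A systematic seasonal difference between cohorts would add to this. The document gives no means of sizing it.

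**Precision of the alternatives for a between-group contrast.** CI width is relative to the unadjusted later titer on the log scale. It is √(1 − rho²) for ANCOVA on log Day 0 titer and √(2(1 − rho)) for simple change from Day 0. The small cost of estimating the slope is ignored.

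| Assumed rho | ANCOVA | Simple change |
|---|---|---|
| 0.3 | 0.95 | 1.18 |
| 0.5 | 0.87 | 1.00 |
| 0.7 | 0.71 | 0.77 |

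ANCOVA is never wider in this calculation. Simple change is wider than the unadjusted titer whenever rho is below 0.5. The fold-rise is worth reporting because it describes the rise within each dose group, not because it sharpens comparisons between groups.

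**The case against.** The case against is substantial. Day 0 is itself a reported outcome day, and individual log values are part of the outcome. Baseline will therefore stand beside every later value, and within-subject change can be derived by anyone. Nothing in the protocol excludes a fold-rise or an adjusted mean, and such detail usually sits in a statistical analysis plan, which is not at hand. The analysis is descriptive. No test, dose selection or escalation step rests on the GMT; escalation uses safety data only. All of this stands, and it is why the point is a suggested improvement.

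Four stronger readings are tempting, and the document does not support them.

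- A reader might infer that the outcome is fixed as absolute GMT alone. Sections 3.2.2 and 11.1 also name individual log values and Day 0.
- A reader might extend the point to the Ad35 neutralizing titer. Section 2.3.1 says that pre-existing Ad35 immunity is rare in Africa.
- A reader might suppose that enrollment spans a full seasonal cycle. No enrollment dates are given. The rules support only the minimum of about seven weeks between Groups A and D.
- A reader might expect Day 0 correction to isolate the vaccine effect. It does not remove natural boosting during follow-up. The concurrent placebo subjects are needed for that, and there are only two per cohort.

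What remains is that a derivable quantity is not a named one. Section 11.2 promises estimates with intervals, and for immunogenicity by dosage the baseline-referenced estimate is the more informative one.

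**Conclusion.** The point holds as a low-cost improvement for CS antibody only. It merits a recommendation at most, with moderate confidence. The protocol names titer levels and no baseline-referenced estimate, in an exposed population whose dose groups are sequential and not randomized against each other. Differences in later GMT between dose groups can therefore partly reflect Day 0.

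Under the assumed SDs and a rho of 0.3 to 0.7, the one-SE carry-over between two dose groups is about 1.1- to 1.4-fold. That is modest beside a large vaccine response and could be misleading if responses are small or the dose groups lie close together. Three things are inferred or assumed: that CS antibody is present at Day 0 (likely from the setting, but no level is given), the SD, and the correlation.

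**What to change.** In sections 3.2.2 and 11.1, or in the statistical analysis plan if it does not already provide this, add for CS antibody:

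1. The within-subject geometric mean fold-rise from Day 0, with 95% CI, at days 28, 56, 84, 112 and 140, by dose group and for pooled placebo.
2. For any between-group display or comparison (dose groups, or vaccine against pooled placebo), GMTs adjusted for log Day 0 titer by ANCOVA on the log scale.
3. The absolute GMTs and individual log values, kept as supporting tables.

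State beside these tables that Day 0 adjustment does not account for natural boosting during follow-up, and show the placebo values at the same days for that purpose.

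The cost is a few sentences. Day 0 serum is already drawn and the Day 0 CS titer is already an outcome, so no sample, visit or subject is added.
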